### Data collection methods

Data will be collected using REDCap (Vanderbilt, TN, USA) database developed questionnaires to gather baseline demographic and clinical details (including mechanism, date, time of injury, time to presentation, vaccination status, medical/surgical history, Fitz-Patrick skin type) and assess pain, itch, feasibility, resource use and cost and scar development (Fig. 1). The E-Burn mobile application in combination with photographs will be used to accurately assess TBSA down to 0.1% which is particularly important given most burns will be small TBSAs [47]. E-burn will be used as it is a validated app for TBSA assessment, reducing the risk of human error [48].

Burn depth will be categorized by both laser Doppler imager (LDI) scans and treating consultant review of photographs (taken using a Fujifilm x-T3 camera with a 60-mm lens) at presentation and the first dressing change (between days 3 and 7). The burn will be defined as either ‘superficial partial thickness only’, ‘mixed depth’ or ‘deep dermal partial thickness only’. The photograph review will be blinded.

### Data management/confidentiality

Each participant involved in the study will be de-identified and allocated a unique identifier. Data will be stored in a de-identified manner either online via REDCap and the Griffith Research Space or onsite in a locked cabinet at the Children’s Centre for Health Research.

### Data analysis

Continuous data will be summarised as either mean (standard deviation) or median (interquartile range) depending on distribution, whilst categorical data will be summarised as frequency (percentage). Feasibility outcomes will be presented descriptively as frequency and percentage. Data will be compared between-groups using linear regression (continuous outcomes), logistic regression (binary outcomes) or Poisson regression (count outcomes). In all cases, treatment group will be included as a fixed effect in the analysis model. Stratification variables will be included as covariables when appropriate. The assumptions for each model will be tested, and if model assumptions are not met, comparisons will be made using non-parametric methods. The effect estimates for each model will be presented as mean difference (continuous outcomes), odds ratio (binary outcomes) and incidence rate ratio (count outcomes), although with 95% confidence intervals. The between-group difference between binary outcomes may also be presented as an absolute difference when appropriate. There will be no formal statistical hypothesis testing.

When the outcome variable is measured repeatedly, for example pain, we will use multilevel mixed effects models to account for the likely non-independent of the repeated measures from each participant. In these situations treatment group and time will be included as fixed effects, with a group-by-time interaction.

An intention-to-treat analysis is preferred as it compares all subjects in the groups to which they were originally randomly assigned (despite withdrawal, treatment failure or cross-over). However, we will also conduct per protocol analyses to assess the potential effect of complying to treatment.

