## Abstract

**Introduction:**

The goal of paediatric hand and foot burn management is hypertrophic scar and/or contracture prevention. The risk of scar formation may be minimised by integrating negative pressure wound therapy (NPWT) as an acute care adjunct as it decreases the time to re-epithelialisation. NPWT has known associated therapeutic burden; however, this burden is hypothesised to be outweighed by an increased likelihood of hypertrophic scar prevention. This study will assess the feasibility, acceptability and safety of NPWT in paediatric hand and foot burns with secondary outcomes of time to re-epithelialisation, pain, itch, cost and scar formation.

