#### Cost analysis

A record of the resources and associated cost (costed at market rate) for each participant will be recorded. This will include treatment costs (e.g. the number of dressing changes, type and size of dressings used, scar therapy products) as well as other burn-related resources (and costs) that may be important to a health service deciding which of the interventions to implement in their burn care model. Number of admissions, length of stay, number of operations and clinic appointments will be recorded and costed at hospital projections (i.e. price of hospital bed per night, hourly theatre rate). Labour time (e.g. occupational therapists, physiotherapist, nurses and surgeons) will be quantified for each patient (on the basis of time duration utilised and number of appointments required) and costed at the relevant state award rates for each respective discipline. This data will be recorded with each presentation to hospital.

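### One distribution-driven rule covers all continuous outcomes with no stated exception for cost, so a skewed cost outcome could lose its mean difference

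*Protocol article*

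**What the plan says.** The Abstract of the protocol article names cost among the "secondary outcomes of time to re-epithelialisation, pain, itch, cost and scar formation". The Cost analysis section explains how resources will be recorded and priced for each child: dressings, scar products, admissions, length of stay, operations, clinic visits and staff time. It also includes "other burn-related resources (and costs) that may be important to a health service deciding which of the interventions to implement". It names no estimator for comparing cost between arms.

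The Data analysis section gives the only analysis rule shown. For description: "Continuous data will be summarised as either mean (standard deviation) or median (interquartile range) depending on distribution". For comparison, the default for a continuous outcome is linear regression, reported as a mean difference with a 95% confidence interval. Then: "The assumptions for each model will be tested, and if model assumptions are not met, comparisons will be made using non-parametric methods". The same section adds: "There will be no formal statistical hypothesis testing". Cost is not mentioned there, either as included or as excepted.

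**The concern.** For most continuous outcomes, a median and a non-parametric comparison are a reasonable response to skew. Cost is different. A service's total cost is the arithmetic mean per child multiplied by the number of children. Neither a median nor a rank statistic can be converted into that total.

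Skew in cost is likely here. The Introduction describes hand and foot burns as mostly treated without admission, with a subcohort that needs admission, surgery and long follow-up. The Cost analysis section prices exactly those items, and under Intervention, children who need grafting stay in the study. A test of model assumptions would therefore often fail for cost.

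The two arms may also differ in ways that medians and means weigh differently. NPWT is added on top of standard dressings, which raises the typical cost. Any saving would come from fewer expensive courses, which move the mean but hardly move the median. Since no formal testing is planned, the estimate and its interval are the whole cost result. If that estimate is not a mean difference, the larger trial mentioned in the Discussion inherits a cost figure that does not bear on total cost.

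**Working it through.** The documents give no cost figures, so there is no stated value to reproduce. All costs below are assumptions in arbitrary currency units. The 15 per arm comes from the Trial design section.

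**1. General form.** Let every child have a base cost B, let NPWT add A to every child in its arm, and let an expensive course add T. Suppose a of 15 control children and b of 15 NPWT children have an expensive course, with a and b both at most 7.
- Median difference (NPWT minus control) = A, whatever a, b and T are.
- Mean difference = A − (a − b) × T / 15.
- Probability that a random NPWT child costs more than a random control child = 1 − a × (15 − b) / 225, when A is positive and smaller than T.

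The mean and the median therefore point in opposite directions whenever 0 < A < (a − b) × T / 15.

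**2. One illustration.** B = 1,000, A = 800, T = 11,000, a = 4, b = 2.
- Control mean = (11 × 1,000 + 4 × 12,000) / 15 = 3,933; median 1,000.
- NPWT mean = (13 × 1,800 + 2 × 12,800) / 15 = 3,267; median 1,800.
- Mean difference = −667 (NPWT cheaper); median difference = +800 (NPWT dearer).
- Rank comparison = 1 − 4 × 13 / 225 = 0.77, which also points to NPWT as dearer.

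**3. How precise the mean difference is.** In this illustration the arm SDs are 5,035 and 3,871, so SE = √((5,035² + 3,871²) / 15) = 1,640. With about 26 Welch degrees of freedom (t = 2.05), the 95% CI is −667 ± 3,369, or about −4,036 to +2,702. The right estimand does not settle which arm is cheaper at this sample size.

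**4. Range of assumptions.** The grid took (a, b) from (2,1), (3,1), (3,2), (4,2) and (4,3), T from 5,000, 11,000 and 20,000, and A from 400, 800 and 1,500, which gives 45 settings.

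| Expensive courses avoided (a − b) | Settings | Mean favours NPWT, median and ranks favour control |
|---|---|---|
| 1 | 27 | 9 |
| 2 | 18 | 12 |
| Total | 45 | 21 |

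In the other 24 settings NPWT is dearer on all three measures.

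**5. Would the fallback be triggered?** Simulated trials (3,000 per scenario, 15 per arm) used a log-normal base cost plus an occasional expensive episode. In four scenarios where NPWT was truly cheaper on the mean, by 200 to 850, a Shapiro-Wilk test on the residuals rejected normality in 94% to 99.9% of trials. The NPWT median was the higher one in 94% to 98%, and the mean and median differences had opposite signs in 52% to 61%. In a fifth scenario, with equal episode rates and NPWT truly dearer by 500, the signs still differed in 38% of trials, because the observed mean difference is itself unstable with 15 per arm.

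**The case against.** The strongest reply is that the Data analysis section does not prescribe a median or rank comparison for cost. Its default effect measure is already the mean difference, the switch is conditional, and "if model assumptions are not met, comparisons will be made using non-parametric methods" does not say ranks. A bootstrap interval for a mean difference is itself non-parametric, and the commitment to estimates with intervals instead of tests fits that reading. The either/or of mean and median concerns description. A statistical analysis plan or health-economic plan that is not shown could also name the cost estimator. All of this stands. A reader might infer that the protocol commits the trial to the wrong cost measure; the text supports only that it permits it.

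Two other stronger readings also fail. A reader might infer that this pilot's cost comparison is meant to decide implementation, since the Cost analysis section refers to what "may be important to a health service deciding which of the interventions to implement in their burn care model". In context that phrase describes which resources will be recorded. The Sample size section says the study is not powered for secondary outcomes, and the list of secondary objectives under Hypothesis and objectives omits cost. A reader might also infer that the rule works against the trial's own case. That case is feasibility, acceptability and safety, not cost saving.

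Finally, the size of any reversal rests on invented costs and on one or two expensive children. The Introduction's remark about outpatient care concerns hand and foot burns in general, whereas eligibility selects more significant burns and excludes TBSA above 10%. Skew is plausible, but its degree is unknown.

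What survives is that the document states a general rule, cost falls within its terms, and the most common ways of applying its fallback would discard the quantity that matters for cost.

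**Conclusion.** The point holds as a modest improvement to a secondary outcome. The stated rule has no exception for cost. If its fallback is applied to cost as a median or rank comparison, the result does not estimate the mean cost difference and may point the opposite way. Under the assumed costs the direction reversed in 21 of 45 settings, so reversal is a real possibility and not a prediction. The conclusion rests on three assumptions: that cost is governed by the general rule because no other is shown, that cost is right-skewed enough to trigger the fallback, and that the fallback is read as medians or ranks. The consequence is confined to the cost result and its use in planning the larger trial.

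**What to change.** Add one sentence to Data analysis or Cost analysis, for example: *Cost will be reported as the arithmetic mean per randomised child by arm, with the mean difference and a bootstrap 95% confidence interval, whatever the distribution; median (IQR) will be given as description only.* Also describe the cost result as exploratory input to the larger trial.

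This needs no new data and only a few lines of code. The downside is a wide interval with about 15 children per arm, which is the true precision and should be shown.

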### Qualitative data

For feasibility outcomes, researchers will undertake a brief thematic analysis [49] on open-ended questions built into questionnaires, to draw out important common themes relating to the study question, which will not be directly captured through the quantitative measures. We will use specific qualitative data analysis software, NVivo 12, for additional insight and to help identify trends in unstructured data.

### Trial monitoring

The Human Research Ethics Committee will be contacted of any adverse events. In addition, a notification of any adverse outcomes to an external regulatory board comprised of burns clinicians independent of the trial will be completed to ensure nil modifications or trial cessation is required. Regular team meetings will be held where the principal investigators will review study progress, address pertinent issues and identify further actions to take. The principal investigators will ensure, via this regulatory review process, that data is managed appropriately (i.e. stored in a de-identified fashion) and that appropriate steps are taken with regard to data cleansing and dissemination of results.

### Access to data

De-identified data will be available on request after appropriate ethics approval.

### Patient and public involvement

This study was guided by previous patient experience of NPWT, identifying barriers and trying to optimise or better understand these barriers [27]. The patients email address will be collected at recruitment so the results of the study may be disseminated to the participant.

## Discussion

In 2020, our team published a RCT which showed that the use of NPWT in paediatric burns decreased time to burn re-epithelialisation by 22% (95% CI 7–34%) [27]. It is acknowledged however that the establishment of efficacy does not correspond to intervention implementation.

Implementation literature suggests that after the efficacy of an intervention is established, only 50% result in clinical uptake. Of that 50%, the average time to routine care model integration is 17–20 years [50]. Often the problem in uptake is the clinical context and the barriers and challenges of the proposed home environment rather than a lack of evidence to support the intervention [50].

Throughout our centre’s first RCT, we identified barriers to utilising NPWT including the bulk of the device, the ability to mobilise and attend to routine activities of daily care, mechanical issues, the perceived extra work load for clinicians and the paucity of knowledge on how to appropriately apply the intervention [27]. These barriers are instant challenges and, despite the now known efficacy of NPWT, make it less likely that NPWT would be integrated into routine burn care.

This study is therefore primarily a pilot feasibility study on the barriers to NPWT. This will help characterise the barriers in depth with a hope to modify and/or minimise them moving forward. The results of this study will help guide the study design and development of a larger national implementation trial of NPWT in paediatric burn care.

## Data Availability

Not applicable for protocol manuscript.

## Abbreviations

NPWT: Negative pressure wound therapy
TBSA: Total body surface area
QoL: Quality of life
RCT: Randomised control trial
PLCBC: Pegg Leditschke Children’s Burns Centre
ED: Emergency Department
PICU: Paediatric Intensive Care Unit
FPS-R: Faces Pain Scale Revised
P-NRS: Pain Number Ranking Scale
FLACC: Face, legs, activity, cry, consolability
I-NRS: Itch Number Ranking Scale
BBSIP: Brisbane based scar impact profile
LDI: Laser Doppler imaging
